#### Sample size

2.5.3

Based on the following formula and our preliminary experimental results of the primary outcome measures (VAS), with a significance level of *α* = 0.05, test power (1-*β*) = 0.9, a mean difference of 1.15, and a variance index of 1.48, it was determined that 20 participants per group are required. To account for an estimated attrition rate of 120%, a total of 48 cLBP participants will be recruited. To compare the effects after the intervention of the two groups, twenty-four right-handed healthy individuals with no history of cLBP were recruited.

$$N={\left[\frac{(t_{\alpha ∕2}+t_{\beta })S}{\delta }\right]}^{2}$$

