**Methods:**

This study is a randomized, double-blind, controlled trial. Forty-eight individuals aged 20 to 55 years with cLBP will be randomly assigned to receive either (1) a 3-week DLPFC-tDCS intervention (*n* = 24) or (2) a 3-week M1-tDCS intervention (*n* = 24), administered four times per week for a total of 12 sessions. Clinical outcomes will be assessed at baseline, 3 weeks, and 6 and 12 months after randomization. Primary outcomes include pain intensity, disability, and scores on the Hamilton Depression and Hamilton Anxiety scales. Secondary outcomes include surface electromyography characteristics of trunk muscles, oxygenated and deoxygenated hemoglobin concentrations in the M1 and DLPFC, and functional connectivity between these two brain regions. These outcomes will be evaluated before and after the intervention. Effect sizes and a mixed-model repeated measures analysis of variance (2 groups × 4 time points) will be calculated.

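### The sample size for a two-arm comparison comes from a one-sample formula, so the stated 90% power is wrong as written

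*Protocol article*

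**What the plan says.** Section 2.5.3 bases the sample size on VAS pain, using preliminary results that are not shown. It works "with a significance level of *α* = 0.05" and "test power (1-*β*) = 0.9", and goes on: "a mean difference of 1.15, and a variance index of 1.48, it was determined that 20 participants per group are required". The printed formula is N = [(t at α/2 + t at β) × S / δ]², and the result is read as a size per group. The section then continues: "To account for an estimated attrition rate of 120%, a total of 48 cLBP participants will be recruited".

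The design is two parallel arms. According to the Abstract, participants "will be randomly assigned to receive either (1) a 3-week DLPFC-tDCS intervention" or an M1-tDCS intervention, 24 in each. Section 2.6 allocates ranks 1–24 to one arm and 25–48 to the other. Section 2.1 places the primary evaluation at 3 weeks, and section 2.11.1 plans a repeated-measures ANOVA with 2 groups and 4 time points.

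**The concern.** The printed formula gives the size of a single sample, or the number of pairs, needed to detect a mean of δ when S is the SD of the single measurement or of the paired difference. A difference between two independent means has twice the variance of one mean, so the per-group formula carries a factor of 2. Without it, each arm is about half the size needed for the stated power, if S is the per-arm SD.

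VAS is the only outcome with a power statement. Both arms receive active tDCS plus sling exercise, so a null between-arm result is plausible. Readers would take such a result as a null with 90% power, when the chance of missing a true difference of 1.15 cm could be a quarter to a third instead of one in ten.

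**Working it through.** **Inputs (section 2.5.3).** α = 0.05; two-sided, because the formula uses α/2; power 0.90; δ = 1.15; S = 1.48; stated result 20 per group; recruited 24 per group.

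**1. Reproduce the plan's figure.** (S/δ)² = (1.48/1.15)² = 1.656.
- Normal quantiles: (1.960 + 1.282)² × 1.656 = 17.4, so 18.
- t quantiles on 19 df: (2.093 + 1.328)² × 1.656 = 19.4, so 20.

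The t version returns the stated 20. The formula was therefore used as printed, with 1.48 entered directly as S.

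**2. The same inputs in a two-arm comparison,** with 1.48 as the per-arm SD and 1.15 as the between-arm difference.
- Normal approximation: n per arm = 2 × 17.40 = 34.8, so 35.
- Exact t-test: 36 per arm (power 90.2%).

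Power uses the noncentral t with 2n − 2 df and noncentrality 1.15 / (1.48 × √(2/n)):

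| Evaluable per arm | Noncentrality | Power | Difference detectable with 90% power |
|---|---|---|---|
| 20 | 2.457 | 66.8% | 1.56 cm |
| 24 | 2.692 | 75.0% | 1.41 cm |

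**3. If 1.48 is a variance.** The SD is √1.48 = 1.217. The printed formula then gives 13.8, so 14, which is not the stated figure. Two-sample power would be 83.0% at 20 per arm and 89.4% at 24, with 25 per arm needed for 90%.

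**4. If 1.15 and 1.48 describe a within-group change.** The printed formula is then the right one for that question. But the question is whether one arm changes from baseline, not whether the arms differ, and no between-arm power follows from it.

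**5. Baseline-adjusted week-3 comparison.** The residual SD is 1.48 × √(1 − r²), where r is the correlation of baseline with week-3 VAS. The documents do not give r, so the values below are assumptions (2n − 3 df):

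| r | 20 per arm | 24 per arm |
|---|---|---|
| 0.5 | 79% | 86% |
| 0.6 | 85% | 91% |

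By the normal approximation, 90% needs r = √(1 − 20/34.8) = 0.65 at 20 per arm, or √(1 − 24/34.8) = 0.56 at 24.

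**6. Attrition.** The step from 20 to 24 is 20 × 1.2. A loss of 20% would need 20/0.8 = 25 per arm, since 24 × 0.8 = 19.2. The 24 recruited cover a loss of 1 − 20/24 = 16.7%, that is 4 of 24.

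**The case against.** The strongest reply is that reproducing 20 shows which number was entered as S, not what that number measures. If S were the combined SD, √(s₁² + s₂²), the factor of 2 would already sit inside S², and the printed formula would be a valid per-group formula for two independent arms. Each arm's SD would then be 1.48/√2 = 1.05, with power of 92.3% at 20 per arm and 96.1% at 24. Nothing in the article defines S this way and it is not the usual meaning of the symbol. With two-sample degrees of freedom the formula gives 18.4, so 19; only n − 1 df gives 20. The reply does not rescue the text, but it does show that the power figure depends on an undefined input.

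A second reply also stands. The 67% and 75% belong to an unadjusted t-test at one time point, whereas section 2.11.1 plans a 2 × 4 repeated-measures ANOVA. The power of that analysis cannot be computed, because no correlation between time points is given. The chance of missing the difference is one in three only at 20 evaluable per arm; with all 24 it is one in four.

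Third, a reader might infer from the 120% that the allowance for dropout is badly wrong. The text does not support that. The figure is evidently a slip for a multiplier of 1.2, and the proper inflation for a 20% loss changes the arm from 24 to 25.

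**Conclusion.** Wrong as written. Section 2.5.3 sizes two independent arms with a formula that, on the ordinary meaning of its symbols, is for one sample or for pairs, and the 90% does not follow for the between-arm comparison. On the ordinary reading, which is also one on which the printed formula returns 20, power is 67% with 20 evaluable per arm and 75% with 24. This rests on three assumptions: 1.48 is the per-arm SD, 1.15 is a between-arm difference, and the test is unadjusted and two-sided at a single time point.

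It is tempting to say flatly that the trial's true power is 67%. The article does not support that, because it defines neither S nor δ and plans a different analysis. What is established is that the formula does not match the design as written, and that the inputs must be defined before any power can be claimed. The attrition figure is a secondary correction of wording.

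**What to change.** Amend section 2.5.3 and keep 48 participants.

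1. State from the preliminary data what S and δ are: SD or variance, per-arm or of a change, between-arm or within-arm. The label should follow those data and not be chosen to fit the result.
2. Replace the formula with the one for two independent samples, n per arm = 2 × [(t at α/2 + t at β) × S / δ]².
3. Restate the power, or the difference detectable with 90% power, for 20 to 24 evaluable per arm. If 1.48 is the per-arm SD, these are 67% to 75%, or 1.56 to 1.41 cm.
4. Make the week-3 VAS comparison baseline-adjusted, using the baseline VAS already collected, and state its power with the correlation from the pilot. For example, at r = 0.5 (an assumption) it is 79% at 20 per arm and 86% at 24.
5. Replace the 120% attrition rate with the loss that 24 per arm covers: 4 of 24, or 16.7%.

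The cost is a wording amendment, a specified covariate and probably a less favourable stated power. No participants or visits are added. If the sponsor wants to keep 90% for an unadjusted comparison on the ordinary reading, the alternative is 36 evaluable per arm; with a 20% loss that is 36/0.8 = 45 per arm, 90 in total.

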This study primarily aims to assess the role of M1-DLPFC functional connectivity in regulating trunk muscle synergy patterns in cLBP patients. The primary hypothesis proposes that abnormal trunk muscle synergy in cLBP is associated with reduced M1-DLPFC functional connectivity. The secondary objective is to evaluate the effects of M1-tDCS and DLPFC-tDCS post-intervention and at follow-up in terms of (1) pain, (2) disability, (3) mental health, (4) surface electromyography characteristics of trunk muscles, and (5) the concentration of oxygenated and deoxygenated hemoglobin in the cerebral cortex of M1 and DLPFC. The secondary hypothesis is that DLPFC-tDCS is more effective than M1-tDCS in increasing M1-DLPFC functional connectivity and improving symptoms of depression and anxiety.

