#### Statistical analysis

2.11.1

Statistical analyses will be performed using SPSS (version 25.0, IBM, USA). Before performing descriptive statistics, the Shapiro–Wilk test will be applied to evaluate the normality of data distribution. Data following a normal distribution will be reported as mean and standard deviation (SD), while non-normally distributed data will be expressed as medians with interquartile range (IQR). Categorical variables will be summarized as percentages and frequencies. Baseline demographic and clinical characteristics will be compared between groups using appropriate statistical tests based on the data type. Continuous variables that follow normal distribution will be analyzed while using independent sample *t*-tests, whereas non-parametric Mann–Whitney *U*-tests will be applied for non-normally distributed continuous data. Categorical variables will be analyzed using chi-square tests or Fisher’s exact tests, as appropriate. Correlations between variables will be evaluated using the Pearson correlation coefficient or Spearman correlation coefficient based on the type of data. A repeated-measures analysis of variance (2 groups × 4 time points) will be performed to assess the therapeutic effects on primary and secondary outcomes. If a significant main effect was observed, *post hoc* tests with Bonferroni correction were conducted. A *p*-value of <0.05 will be considered statistically significant.

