### Summary

3.1

This study presents the protocol for an RCT designed to assess the efficacy of tDCS targeting the DLPFC in patients with cLBP. The trial aims to determine whether DLPFC-tDCS can improve activity and functional connectivity between the M1 and DLPFC. The results of this study will provide critical insights into the potential therapeutic role of DLPFC-tDCS in improving M1-DLPFC connectivity and trunk muscle synergy, forming a theoretical foundation for novel treatment approaches for cLBP. Previous research has used multivariate pattern analysis and fMRI to identify disruptions in functional connectivity among key brain networks in cLBP patients. These networks include salience, sensorimotor, the default mode, and central executive networks. Findings suggest that the rostral anterior cingulate cortex and medial prefrontal cortex may serve as critical hubs associating the default mode network with other neural circuits in individuals with cLBP (Tu et al., 2019). Furthermore, a study published in *NeuroImage* demonstrated that the DLPFC has extensive anatomical projections to M1 and that these two regions interact closely during motor tasks. This suggests that exercise-induced neuroplasticity may result from altered input from the DLPFC to M1 rather than the training effect within M1 itself (Cao et al., 2022). These findings highlight the relevance of M1-DLPFC functional connectivity in motor control and muscle coordination.

To the best of our knowledge, this study will be the first to investigate the pathological mechanisms of cLBP by examining brain connectivity and trunk muscle synergy. We hypothesize that the abnormal coordination patterns observed in trunk muscles in cLBP patients are not only a result of adaptive changes within M1 and DLPFC but also due to reduced functional connectivity between these regions. This connectivity impairment may play a key role in the neuromuscular dysregulation of trunk muscles in cLBP. By comparing the therapeutic effects of M1-tDCS and DLPFC-tDCS, we expect that M1-tDCS will primarily increase M1-supplementary motor area (SMA) connectivity, while DLPFC-tDCS will strengthen M1-DLPFC functional connectivity. This improvement in connectivity is expected to restore trunk muscle coordination and improve clinical symptoms.

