### Strengths and limitations

3.2

One of the major strengths of this protocol is that it represents one of the first clinical trials investigating the efficacy of DLPFC-targeted tDCS in patients with cLBP. If proven effective, DLPFC-tDCS could serve as a viable therapeutic option for managing cLBP. Another advantage of the study is its potential to reveal the neuroregulatory mechanisms underlying the functional connections between brain regions and their impact on trunk muscle coordination in cLBP patients.

However, there will be some limitations. A key limitation is the absence of a healthy control group. Including healthy participants would allow for a more comprehensive comparison with the M1-tDCS and DLPFC-tDCS groups, improving the interpretation of the results. Moreover, differences in the sampling rates of the two fNIRS systems used during measurements present a methodological challenge. Since the sampling rates of fNIRS and sEMG differ, direct correlation analyses between their signals cannot be performed. Instead, only data-level analyses can be conducted, which may limit the ability to fully capture the relationship between cortical activity and muscle activation patterns.

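### The healthy group is given only a post-treatment comparison, so the plan states no contrast that could show patients' synergy to be abnormal or their connectivity reduced before treatment

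*Protocol article*

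**What the plan says.** - **Primary hypothesis (Introduction):** "The primary hypothesis proposes that abnormal trunk muscle synergy in cLBP is associated with reduced M1-DLPFC functional connectivity".
- **Healthy group (2.5.3 Sample size):** "To compare the effects after the intervention of the two groups, twenty-four right-handed healthy individuals with no history of cLBP were recruited". The article states no other use or time point for these people.
- **Limitations (3.2):** "A key limitation is the absence of a healthy control group". This contradicts 2.5.3.
- **Treatment (2.8):** every patient receives active tDCS plus sling exercise, 12 sessions over 3 weeks. There is no sham or untreated arm.
- **Expected effect (3.1 Summary):** M1-tDCS should mainly raise connectivity between M1 and the supplementary motor area, and DLPFC-tDCS should strengthen M1-DLPFC connectivity. The text then adds: "This improvement in connectivity is expected to restore trunk muscle coordination and improve clinical symptoms".
- **Timing of the sEMG, fNIRS and connectivity measures (Abstract, Methods):** "These outcomes will be evaluated before and after the intervention".
- **Analysis (2.11.1):** "A repeated-measures analysis of variance (2 groups × 4 time points) will be performed to assess the therapeutic effects on primary and secondary outcomes". Also: "Correlations between variables will be evaluated using the Pearson correlation coefficient or Spearman correlation coefficient based on the type of data". Neither sentence mentions healthy people, and the second names neither variables nor a time point.

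**The concern.** Abnormal and reduced are comparative words. To use them of patients, one must show that patients differ from healthy people while the disease state is still untreated. The only comparison with healthy people that the article states comes after 12 sessions of a treatment meant to move these same measures towards normal. With two active arms, no untreated patients remain at that point.

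What is at stake is the interpretation of the primary hypothesis. Suppose treated patients do not differ detectably from healthy people. That result fits a deficit that was corrected, a deficit that never existed, and a comparison too small to see what is left. Only the baseline contrast can separate the first two. The randomised comparison of the two stimulation sites is not affected.

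**Working it through.** **1. The plan's own figure.** The only sample size stated is for pain on the VAS. The printed formula is N = [(t_α/2 + t_β) S/δ]², with α = 0.05, power 0.9, S = 1.48 and δ = 1.15. Using t quantiles on 19 degrees of freedom: [(2.093 + 1.328) × 1.48/1.15]² = 19.4, rounded up to 20. Then 20 × 1.2 = 24 per arm, 48 in all. The stated figure reproduces. It says nothing about the 24 healthy people or the primary hypothesis, for which no power is given.

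**2. What each part of the hypothesis needs.**

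| Element | Data needed | Stated in the article? |
|---|---|---|
| Synergy is abnormal | Untreated patients v healthy | No |
| M1-DLPFC connectivity is reduced | Untreated patients v healthy | No |
| The two are associated | Both measures in the same patients, best before treatment | Partly: correlations planned, variables and visit not named |
| Treated patients approach healthy values | Treated patients v healthy | Yes, as a purpose in 2.5.3; no analysis in 2.11.1 |

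The patients' half of the first two rows will be collected, because these outcomes are measured before the intervention as well as after it.

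**3. Illustration of the loss of power.** From the document: group sizes 48, 24 and 24, and α = 0.05 (two-sided, from the α/2 term). Assumed: the untreated deficit D in SD units and the fraction f that treatment removes. The method is a two-sample t-test with noncentrality λ = D(1 − f) × √[n₁n₂/(n₁ + n₂)].

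- 48 v 24: √(1152/72) = 4, with 70 degrees of freedom and critical value 1.994.
- 24 v 24: √(576/48) = 3.464, with 46 degrees of freedom and critical value 2.013.

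For D = 0.8 at baseline with 48 v 24, λ = 3.2 and power is 0.88. With f = 0.5, λ = 1.6 and power is 0.35.

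| Assumed D | Baseline, 48 v 24 | Half removed, 48 v 24 | Half removed, one arm, 24 v 24 | Three quarters removed, 48 v 24 |
|---|---|---|---|---|
| 0.5 | 0.51 | 0.17 | 0.14 | 0.08 |
| 0.8 | 0.88 | 0.35 | 0.27 | 0.12 |
| 1.0 | 0.98 | 0.51 | 0.40 | 0.17 |

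With full restoration the rejection rate falls to α, 0.05.

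**4. The same illustration following section 3.1.** The pooled columns shrink the deficit equally in both arms, whereas section 3.1 expects M1-DLPFC strengthening from DLPFC-tDCS. Take D = 0.8 with half removed in the DLPFC arm only. The DLPFC arm against healthy (24 v 24, difference 0.4) has power 0.27. The M1 arm against healthy (24 v 24, difference 0.8) keeps 0.77. Pooled, the mean difference is (0.4 + 0.8)/2 = 0.6, so λ = 2.4 and power is about 0.66, ignoring the small extra spread from mixing the arms. The loss is thus concentrated in the DLPFC arm.

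**The case against.** A reader might infer that the plan defeats itself: that the better treatment works, the less the primary hypothesis can be confirmed. The documents do not support that, for four reasons.

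- **The contrast is not named as the test of the primary hypothesis.** The sentence in 2.5.3 speaks of effects after the intervention. It can fairly be read as a benchmark for how far treated patients have normalised, and post-treatment timing suits that use.
- **The hypothesis is an association.** It says that "abnormal trunk muscle synergy in cLBP is associated with reduced M1-DLPFC functional connectivity". A correlation can be examined in baseline patient data without healthy people.
- **Section 3.1 does not expect the same change in both arms.** Equal shrinkage of the M1-DLPFC deficit is therefore an assumption, as are the 0.8 SD deficit and the halving.
- **A baseline contrast is not ruled out.** Pre-treatment patient values will exist, 2.5.3 does not say when the healthy people are measured, and a condensed article may leave detail to the full protocol. The same applies to age and sex matching, whose absence is not a fault here.

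All four points stand, and they limit the finding without removing it. Normalisation presupposes a deficit that has been shown. A correlation among patients can show that two measures vary together, but not that either is abnormal or reduced. And the article does more than stay silent on timing: it fixes a single purpose for the healthy group, and that purpose lies after treatment.

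A further objection is that criticising the time point is premature while section 3.2 says no such group exists. That is fair, and the contradiction must be settled first. Either answer still requires a change: if the group exists, it needs a baseline role; if not, abnormal and reduced have no reference in this trial.

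**Conclusion.** The concern holds in this limited form. As written, the article states no comparison of untreated patients with healthy people, although its primary hypothesis uses words that need one. The stated post-treatment comparison is legitimate as a benchmark, but alone it cannot tell restored from never abnormal, and it weakens as a test of a deficit to the extent that treatment works.

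The direction of that loss does not depend on the assumed figures; its size does. For an assumed 0.8 SD deficit with 48 v 24, power falls from about 88% at baseline to about 35% if half the deficit is removed in both arms, or to about 66% if it is halved in the DLPFC arm only. None of these deficits or fractions comes from the documents.

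The change should be made, since it bears on how the primary hypothesis can be read. The contradiction between 2.5.3 and 3.2 on whether a healthy group exists must be resolved with it.

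**What to change.** First reconcile section 2.5.3 (24 healthy individuals recruited) with section 3.2 (no healthy control group).

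**If the group exists**, correct 3.2, and state in 2.5.3 with a matching line in 2.11.1 that:
- abnormality is judged by comparing all 48 patients at baseline with the 24 healthy individuals on M1-DLPFC connectivity and the synergy measures, adjusted for age and sex;
- the association between connectivity and synergy is examined in baseline patient data;
- the post-intervention comparison with healthy people is descriptive, by arm, as differences with 95% confidence intervals, and non-significance is not read as restoration.

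**If the group does not exist**, delete the sentence in 2.5.3 and restate the primary hypothesis as an association within patients, without the claims of abnormal synergy or reduced connectivity.

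**Cost:** a few sentences and, in the first case, one added model per measure. Patients' baseline values are already to be collected, so no new patients or patient visits are needed. The healthy people must have been measured on the same tasks and measures; the article does not say whether they were, and this should be confirmed.
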